## Abstract

**Background::**

More than 80% of the population suffer from low back pain at some time during their lives. An orthopedic device (LSM-01) will be used to alleviate back pain caused by muscle tension. LSM-01, which has a rotating roller, stimulates meridian-muscles around the governor vessel, bladder meridian, and gall bladder meridian.

**Methods::**

This study will be a randomized, single-blinded, sham-controlled, parallel-group, pilot clinical trial. Subjects will be randomly allocated to the treatment group (LSM-01) or the control group (sham device). The duration of the clinical trial will be 2 weeks. The primary outcomes will be measured using the visual analog scale; the secondary outcomes will include pressure pain threshold, Oswestry Disability Index, and Patient Global Impression of Change. Statistical analysis will be performed for the full study population. Analysis of covariance will be conducted to identify differences in pain before and after the application of the device.

**Discussion::**

This clinical trial will evaluate the safety and efficacy of the LSM-01 device. As a pilot study, this investigation includes a limited number of subjects. The results of this pilot trial will form a basis for a large-scale clinical trial, which will be conducted in the future.

**Clinical trial registration::**

This study protocol is registered with the Clinical Research Information Service (CRIS) of Korea. Clinical trial registration number: CRIS-KCT0006425. Registered: October 5, 2021; https://cris.nih.go.kr/cris/search/detailSearch.do?search_lang=E&search_page=L&pageSize=10&page=undefined&seq=20056&status=5&seq_group=20056

## Introduction

1

Back pain is a musculoskeletal abnormality (excluding pain caused by pregnancy or infection), which persists for >3 days in the waist area of the thoracic spine.^[1]^ Chronic back pain refers to pain which persists for >3 months. Pain continues to occur even after the primary damaged tissue has healed.^[2]^ Spinal pain is attributed to numerous reasons, such as severe exercise or accident, spinal disease, aging, wrong posture, and lack of exercise.^[3]^ When resistance to gravity is compromised, the human body attempts to compensate; twisting of the spine changes the gravitational line, leading to an unstable posture. Subsequently, exposure of the musculoskeletal system to more load on 1 side can lead to pain.^[4]^ Most individuals experience spinal pain at least once in their lives. A study reported that the annual prevalence of spinal pain ranges 15% to 45% and 30% on average.^[5]^

In Korean Medicine, governor vessel (GV), bladder meridian (BL), and gall bladder meridian (GB) are important treatment target for chronic low back pain (LBP).^[6]^ The efficacy of various Korean Medical interventions, such as Thread Embedding Therapy^[7]^ and Warm Needle Acupuncture,^[8]^ for LBP are studied using these meridians. These meridian-muscles correspond to the muscular system, such as spinous process, erector spinae muscle, gluteus medius, and tensor fasciae latae. In addition, these muscles are used in the myofascial release technique of Chuna manual therapy to treat chronic LBP.^[9,10]^

LSM-01 has a rotating roller that uses electricity to stimulate the meridian-muscles around GV3, GV4, GV6, GV9, GV12, GV14, GB30, GB31, GB32, GB33, BL13, BL17, BL20, BL23, BL25, BL26, BL42, BL46, BL49, and BL52. It relieves muscle stiffness through mechanical stimulation. The objective of this pilot clinical trial is to evaluate the safety and efficacy of LSM-01 in subjects with LBP compared to sham device.

## Methods

2

### Study design and sample size calculation

2.1

This study was designed as a randomized single-blinded, sham-controlled, parallel-group, pilot clinical trial. The protocol ver 1.1 is approved by the Institutional Review Board (IRB) on July 1, 2021. A total of 30 subjects with LBP will be recruited from the DUCKMH through Banner promotion; the recruitment commenced in June 2021. All subjects will receive a written explanation of the study protocol and an informed consent form by investigator. X-ray and computed tomography (CT) imaging of the L-spine will be performed for those with LBP based on history or physical examination. Additionally, vital signs will also be measured at every visit. For preliminary and parallel-design studies, Julious suggested that the empirically optimal sample size is 12 individuals per group, considering feasibility, estimated average, and dispersion accuracy.^[11]^ Considering a dropout rate of 20%, the calculated sample size for this pilot clinical trial is 30. A total of 30 patients with LBP who meet the eligibility criteria will be randomly assigned to groups in a 1:1 ratio. According to their group, the subjects will be treated with the LSM-01 device or sham device for 2 weeks. The total duration of the clinical trial is 3 to 4 weeks. The total number of visits is 7, and the efficacy and safety of the treatment are assessed at each visit. Subjects are notified of their further visit schedule by the investigator each visit. The administration of pain relievers will be maintained at the same dose and frequency until the end of the clinical trial. The study flow chart is presented in Table 1 and Figure 1.

**Table 1 T1:** Schedule for the enrollment, intervention, and assessments.

	Study period				
	Recruitment	Intervention period			Observation period
Visit	Screening	V1 Before intervention	V1 After intervention	V2–V6	V7
Checking the selection/exclusion criteria	•				
Vital signs	•	•		•	•
Demographic surveys and body measurements	•				
Medical history of lumbar and other body organs	•				
Lumbar spine X-ray and computed tomography (CT)	•				
Physical examination	•				
Random assignment		•			
Treatment (Orthopedic or sham device)		•		•	
Visual Analog Scale	•	•		•	•
Pressure pain threshold		•		•	•
Oswestry Disability Index		•		•	•
Patient Global Impression of Change				•	•
Checking medical history and changes in treatment drugs			•	•	•
Suspending the test and checking the criteria for elimination			•	•	•
Safety assessment			•	•	•

**Figure 1 F1:**
[figure not shown]
Standard Protocol Items: Recommendations for Intervention Trials (SPIRIT) figure show schedule of enrolment, interventions, and assessments. The “X” refers to what is done in the given period.

### Inclusion and exclusion criteria

2.2

The inclusion criteria are as follows: 20 to 70 years of age; visual analog scale (VAS) ≥75 mm; and use of painkillers. The exclusion criteria are as follows: history of spinal fractures; spinal surgery; severe back pain with VAS >75 mm lasting >3 days within 3 months; neurological symptoms of sensory and motor paralysis; abnormalities detected on L-spine X-ray and CT examination; severe pain in other parts of the body; skin diseases; inflammation; presence of wounds around the hip joint of the spine and pelvis; other treatment for back pain except painkillers; cardiovascular disease; tumors; alcoholism; drug abuse; and participation in other clinical trials within 30 days.

### Randomization and blinding procedures

2.3

An independent statistician will randomly assign 15 individuals per group using the statistical program SAS Version 9.4 (SAS Installation. Inc., Cary, NC). Subjects will be assigned using balanced block randomization, without stratification. The clinical trial manager will assign screening numbers to subjects in the order they have provided informed consent. Subjects will be assigned to the experimental group or control group according to their randomization identification code. The information regarding the assignment of intervention will be stored in an independent secure place. The randomization code will be placed in an opaque envelope. The trial investigator will not perform the randomization and assignment of intervention. Therefore, subjects and investigators are blinded. Moreover, the trial investigator will not serve as the operator in this study.

### Device

2.4

The device used in this clinical trial has an electric motor (Fig. 2, Table 2). This second-class medical device is licensed by the Ministry of Food and Drug Safety of Republic of Korea for the purpose of relieving lumbar muscle pain (classification number: A67025.01). We conduct clinical trials using this device to evaluate its safety and efficacy. There is no difference between the LSM-01 and sham device in terms of appearance, vibration, and sound. However, there is a difference in the rotation of the roller (Fig. 3). In the LSM-01, the connection axis between the motor unit and the rotating roller is connected normally. In the sham device, rotational fixing pins and fixed hexagonal pins are missing and prohibit rotation. The feel of the LSM-01 and sham device is similar and blinding is maintained. The LSM-01 and sham device are manufactured by Spine Muscle Strengthening Machine Co. (Namyangju, Republic of Korea).

**Figure 2 F2:**
[figure not shown]
Appearance and size of the device.

**Table 2 T2:** Appearance and description of the device.

(1)	Power cord	Connects power to the main board
(2)	Body cover	For safety, a cover protecting the user's contact part
(3)	Exhaust vent	Ventilates the interior of the device
(4)	Power switch	Turns on/off the device
(5)	Body cover	For safety, a cover protecting the user's contact part
(6)	Cable holder	Fixes the power cable
(7)	Current fuse	Protects the product from excessive current
(8)	Roller	Acts mechanically by direct contact with the human body
(9)	Rotating core	Rotates the roller continuously
(10)	Bearing	Rotates the roller more softly
(11)	Support	Separates roller contact with the human body in each rotation

**Figure 3 F3:**
[figure not shown]
Differences between the LSM-01 and sham device: no fixed bolt and pin.

### Intervention

2.5

Firstly, while the patient is lying in the lateral position, the LSM-01 will be applied to the gluteus medius 30 times (60 s/application). Secondly, in the same position, the LSM-01 with be applied to the tensor fasciae latae 15 times (30 s/application). Finally, while the patient is lying in the supine position, the LSM-01 will be applied to the spinous process of S1, L5, L3, L1, T11, T8, T4, and C7 15 times (30 s/application). The intervention will be repeated twice. A single qualified Korean medical doctor will perform the procedure using the device in both groups. All eligible subjects will receive treatment according to their group (i.e., LSM-01 or sham device). The treatment will be performed thrice weekly for a total of 6 times. During the trial, the use of painkillers will be allowed, whereas other treatments are prohibited.

### Outcome measures

2.6

The primary outcome is the VAS score, which will be used to assess LBP at each visit. The secondary outcomes are the average change in the pressure pain threshold (PPT), Oswestry Disability Index (ODI) score after treatment (V7) compared with baseline (V1), and Patient Global Impression of Change (PGIC). VAS, PPT, ODI, and PGIC will be measured at each visit.

#### VAS

2.6.1

The VAS is used to evaluate the intensity and frequency of pain. The visual reflection scale is used by the patient himself, indicating the degree of pain on a 10-cm horizontal straight.

#### PPT

2.6.2

The PPT is determined by pressing vertically on both sides (BL25) of the subject at a rate of 1 kg/s with a pressure algorithm and measuring the pressure (kg/cm) at the moment the subject first complains of pain.

#### ODI

2.6.3

The ODI indicates dysfunction due to pain. It consists of 6 questions for 10 items, total of 60 question. For each question, subjects use a score from 0 to 5 points, with higher scores indicating greater disability.

#### PGIC

2.6.4

The PGIC evaluates the improvement perceived by the subject after treatment versus baseline using the following answers: “Substantially better,” “A lot better,” “A little better,” “No change,” “A little worse,” “A lot worse,” and “Very much worse.”

### Data collection and monitoring

2.7

At screening, the subjects will complete a questionnaire regarding their sociodemographic characteristics, provide their medical history, and undergo X-ray and CT examinations of the lumbar. When the dropout occurs, outcomes are obtained as possible. Personal information and data will be managed by the investigators. The final trial dataset will be accessible to statisticians and principal investigator (PI) and can be accessible with the permission of the PI. All information regarding the subjects and intervention will be kept confidential. All documents related to the clinical trial will be recorded and classified using an identification code, rather than the name of the subject. An independent contract research organization (CRO) – MEDI CRO Co., Ltd. (Seoul, Republic of Korea) – will monitor the research plans, case records, and annexed documents according to the schedule included in the clinical trial protocol. CRO has no competing interest. The CRO will review all evidence documents related to the clinical trial and perform data quality control. At the end of the trial, the case report forms will be stored in a locked cabinet in accordance with IRB regulations.

### Statistical analysis

2.8

Data analysis, including the validity evaluation variable, will be performed in the full analysis set group. The per protocol group analysis will be performed as the supplementary analysis. An analysis of covariance using the baseline value of VAS as a covariate will be performed. The ambient mean and standard error, 95% confidence interval, *t* statistic, and *P*-value for change in each group will be determined. Variables for the evaluation of efficacy will also be analyzed in the same manner. In all statistical tests, an α = 0.05 on both sides will indicate a statistically significant difference. All statistical analyses will be performed using the SPSS Statistics for Windows Version 20.0 (IBM Corp., Armonk, NY) software. Last observation carried forward analysis will be used to handle missing data. Safety evaluation will be mainly performed by analyzing the frequency of adverse events (AEs) and serious adverse events (SAEs), which are suspected to be associated with the treatment. The evaluation of safety will be conducted in the safety population. An independent sample *t*-test or Wilcoxon rank-sum test will be performed for the analysis of continuous variables. The McNemar test will be used for the analysis of categorical variables. A chi-squared test or Fisher exact test will be performed to examine the potential association of the treatment with the occurrence of AEs.

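### The efficacy analysis attaches its inference to change within each group and never writes the LSM-01 minus sham contrast that the objective calls for

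*Protocol article*

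**What the plan says.** The aim in the Introduction is comparative: to "evaluate the safety and efficacy of LSM-01 in subjects with LBP compared to sham device". Section 2.1 describes the design as a "randomized single-blinded, sham-controlled, parallel-group, pilot clinical trial". Section 2.6 makes VAS the primary outcome: "The primary outcome is the VAS score, which will be used to assess LBP at each visit".

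The analysis is given in section 2.8. The model is stated as "An analysis of covariance using the baseline value of VAS as a covariate will be performed". The listed outputs (a mean, standard error, 95% confidence interval, t statistic and P-value) are then given "for change in each group will be determined". The remaining efficacy measures follow the same route: "Variables for the evaluation of efficacy will also be analyzed in the same manner". Every test is two-sided at 0.05.

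The Methods paragraph of the abstract gives the purpose of the model: "Analysis of covariance will be conducted to identify differences in pain before and after the application of the device". Sham is not mentioned in that sentence.

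One two-sample procedure for continuous data is written out. It comes later in section 2.8, after the sentences on adverse events and the safety population: "An independent sample *t*-test or Wilcoxon rank-sum test will be performed for the analysis of continuous variables". It names neither the variables nor the groups.

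**The concern.** A P-value for change within one arm asks whether pain moved from baseline. It does not ask whether it moved more with the device than with the sham. Subjects enter with a high VAS, so some fall in both arms is plausible without any device effect, through natural course, regression to the mean and response to a sham procedure.

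Two separate within-arm P-values cannot isolate the device effect. A significant fall under LSM-01 is compatible with no effect. So is a significant fall under LSM-01 beside a non-significant one under sham, because the difference between two P-values is not a test of the difference between arms. The article also says that the pilot is to form the basis for a larger trial. The quantity needed for that purpose is the between-group estimate with its interval, which is the one quantity not named.

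**Working it through.** **1. The plan's own figure.** Section 2.1 takes 12 evaluable subjects per group and 20% dropout: 12 / (1 − 0.20) = 15 per group, 30 in total. This reproduces the stated 30. No effect size, SD or power is stated, so there is no power figure to check.

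**2. The text, side by side.**

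| Element | What is written |
|---|---|
| Objective (Introduction) | LSM-01 against sham |
| Design (2.1) | Randomised, sham-controlled, parallel groups |
| Purpose of ANCOVA (abstract) | Pain before against after |
| Model (2.8) | Baseline VAS as covariate; no factor named |
| Inferential output (2.8) | Change, per group |
| Other efficacy variables (2.8) | As for VAS |
| Two-sample t or rank-sum test (2.8) | After the safety text; not tied to VAS |

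The first two rows are comparative. The next four, which define the efficacy analysis, contain no comparison with sham.

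**3. What within-group P-values would do with no device effect.**

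Inputs: n = 15 per arm and two-sided α = 0.05 (document); common fall δ = 5, 10 or 15 mm and SD of change s = 15 or 20 mm (assumed).

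The within-arm one-sample t-test has 14 degrees of freedom, critical value 2.145 and non-centrality √15 × δ/s. Let p be its power from the non-central t distribution. The arms are independent and fall equally, so the chance of significance with LSM-01 but not with sham is p(1 − p). At these falls, significance in the wrong direction is negligible.

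| Fall δ (mm) | SD s (mm) | δ/s | p: LSM-01 arm significant | p(1 − p): LSM-01 only |
|---|---|---|---|---|
| 5 | 20 | 0.25 | 14.7% | 12.4% |
| 5 | 15 | 0.33 | 22.5% | 17.4% |
| 10 | 20 | 0.50 | 43.8% | 24.6% |
| 10 | 15 | 0.67 | 67.1% | 22.1% |
| 15 | 20 | 0.75 | 77.1% | 17.7% |
| 15 | 15 | 1.00 | 94.9% | 4.8% |

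The LSM-01-only pattern therefore ranges from about 5% to 25%. It cannot exceed 25%, the maximum of p(1 − p), and it shrinks when the fall is large because both arms then become significant. With no fall at all it is 2.4%. With 12 evaluable subjects per arm, the same grid gives about 10% to 25%.

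**4. The comparator.** A between-group test at two-sided 0.05 favours LSM-01 falsely in 2.5% of trials. As a check, an ANCOVA with group and baseline was simulated with no device effect (4,000 runs per scenario; 12 or 15 per arm; common fall 0, 5 or 10 mm; assumed SD 10 mm and baseline/follow-up correlation 0.5). It rejected in 4.6% to 5.8% of runs in either direction, close to the nominal 5%, whatever the common fall.

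**The case against.** The strongest reply is that a between-group test is probably meant. In a two-arm randomised trial, a baseline-adjusted ANCOVA normally has treatment group as its factor; fitted inside one arm it would be an odd choice. The term *ambient* mean may be a mistranslation of adjusted mean, and adjusted means per group are ordinary output beside the group test. The independent t-test or rank-sum sentence also describes a two-sample comparison. A condensed article may leave model details to a fuller document.

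Much of this stands. A reader might infer that the trial will not test LSM-01 against sham at all; the document does not support that. The silence about a treatment factor would be weak evidence on its own. What remains is the wording that is present: section 2.8 assigns the P-value to change per group, and the abstract independently gives a before-after purpose. The two-sample sentence does not repair this. It is not linked to VAS, and if it were meant for efficacy it would be a second test, unranked against the ANCOVA.

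A reader might also infer that a significant LSM-01 arm will be declared efficacy. The document contains no such rule, and its Discussion calls the sample too small for firm conclusions on effectiveness. The error rates above are therefore conditional on within-group P-values being read as results. The article's statement that 95% recover within a few months of onset adds little support, since treatment lasts two weeks.

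**Conclusion.** The point holds as a mismatch between objective and written analysis. For VAS and every other efficacy variable, the stated inference concerns change within each group, and the LSM-01 minus sham contrast is never written. Followed literally, the listed outputs would not answer the trial's question.

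The text finding needs no assumption. The size does: with no device effect, the LSM-01-only pattern would appear in about 5% to 25% of trials at 15 per arm, against 2.5% for a between-group test in that direction. The falls of 5 to 15 mm and the SDs of 15 to 20 mm are assumptions; only the 15 per arm and the 0.05 level come from the document. Because this is a pilot, the between-group estimate and its interval matter more than the P-value, but that estimate still has to be named.

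**What to change.** State in section 2.8, and align the abstract:

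*The primary analysis is an ANCOVA of VAS at V7 (or of the change from V1 to V7) with treatment group as factor and V1 VAS as covariate. The primary result is the adjusted mean difference, LSM-01 minus sham, with its two-sided 95% confidence interval and P-value.*

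With V1 VAS in the model, the V7 value and the change from V1 give the same adjusted difference, so either may be chosen. V1 and V7 are the visits that section 2.6 already uses for secondary outcomes. Present within-group changes as descriptive only, and say that they are not evidence of efficacy. Say which variables the independent t-test or rank-sum sentence covers.

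The cost is two sentences. The within-group P-values, which tend to look more favourable, lose their inferential role. The sample size stays at 30 and no extra data are needed.

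### LOCF is the only missing-data method the article names, with 20% dropout allowed for; if pain is changing over the 2 weeks it can shrink a true VAS difference or create a false one

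*Protocol article*

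**What the plan says.** Section 2.8 of the protocol article (Statistical analysis) sets an analysis of covariance with baseline VAS as covariate, in the full analysis set, tested at two-sided 0.05. On missing data it says: "Last observation carried forward analysis will be used to handle missing data". A supplementary per protocol analysis is also planned. It changes the population and does not test the LOCF assumption.

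Section 2.1 allows for loss: "Considering a dropout rate of 20%, the calculated sample size for this pilot clinical trial is 30". The starting point is that "the empirically optimal sample size is 12 individuals per group", and section 2.3 confirms the allocation: "An independent statistician will randomly assign 15 individuals per group".

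Section 2.6 provides repeated data: "VAS, PPT, ODI, and PGIC will be measured at each visit". For the primary outcome it says: "The primary outcome is the VAS score, which will be used to assess LBP at each visit". It ties the change in PPT and ODI to V7 against V1, but sets no single time point for VAS. Section 2.7 adds that outcomes of dropouts will be obtained where possible.

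**The concern.** LOCF fills each missing later score with the last one seen and then treats it as observed. That is right on average only if the score would have stayed flat. Subjects enter with a VAS of at least 75 mm and are treated over 2 weeks, so change during that time is plausible, although the article does not state it.

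If pain is falling, a subject who leaves early is recorded with too high a final score. The error is larger in the arm that improves more, so a true difference shrinks even when dropout is equal. If one arm loses more subjects than the other, a difference can appear where there is none.

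The trial is a pilot whose results are to form the basis of a larger trial. A distorted VAS difference would be carried into that planning. The method is stated in the article, so this is a choice that can be reviewed and not a detail left to an unseen document.

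**Working it through.** **The plan's own figure.** 12 per group inflated for 20% dropout: 12 / (1 − 0.20) = 15 per group, 2 × 15 = 30. This reproduces the stated size. Expected dropout is 0.20 × 30 = 6, or 3 per arm.

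**Assumed inputs (not in the article).** SD 18 mm; correlation 0.7 between visits; linear improvement of 20 mm from V1 to V7 in both arms; where there is an effect, a further 15 mm in the device arm; dropout after V3, unrelated to outcome; VAS compared at V7.

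**Expected bias.** V3 lies 2/6 of the way from V1 to V7, so a dropout is frozen at 20 × 2/6 = 6.7 mm of improvement and misses 20 − 6.7 = 13.3 mm.

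- No true effect, 3 of 15 lost in one arm and none in the other: 0.2 × 13.3 = 2.7 mm false difference.
- No true effect, 6 of 15 against none: 0.4 × 13.3 = 5.3 mm.
- No true effect, 3 of 15 lost in each arm: 2.7 − 2.7 = 0.
- True effect 15 mm, 3 of 15 lost in each arm: the effect at V3 is 15 × 2/6 = 5 mm, so LOCF estimates 0.8 × 15 + 0.2 × 5 = 13 mm.

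**Precision for scale.** Residual SD after baseline adjustment: 18 × √(1 − 0.7²) = 12.9 mm. SE of the difference: 12.9 × √(2/15) = 4.7 mm.

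**Simulated error rates** (15 per arm, ANCOVA on LOCF data, same assumptions; ranges cover repeated runs):

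| Scenario | Estimate | Rejection rate |
|---|---|---|
| No effect, complete data | 0 | 4.9% |
| No effect, 3 lost per arm | 0 | 3.1 to 3.9% |
| No effect, 3 versus 0 | 2.6 to 2.8 mm | 7.2 to 8.4% |
| No effect, 6 versus 0 | 5.3 mm | 15.4 to 15.8% |
| True 15 mm, complete data | 15 mm | 85% |
| True 15 mm, 3 lost per arm | 13 mm | 63% |

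**A second set of assumptions** (improvement 30 mm with device and 15 mm with sham, or 30 mm in both; subject-specific slopes; dropout spread over the visits). With 20% lost in each arm, a true 15 mm became 13.5 mm and power fell from 75% to 64%; type I error was 5.4%. With 33% lost in one arm and 7% in the other and no true effect, the false difference was 4.0 to 4.4 mm, with type I error of 11 to 12%. Its sign followed the arm with more dropout.

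**Would a mixed model help?** One data set of 3,000 per arm was analysed for each scenario under the second set. At V7 the mixed model gave −0.2 (true 0), −15.2 and −14.8 mm (true −15), where LOCF gave +4.0, −13.6 and −10.3 mm. Dropout there was unrelated to outcome and the model's form matched the data, so this checks bias only. It does not show performance at n = 30.

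**The case against.** Several points on the other side stand.

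- A reader might infer that LOCF is the sole method for the trial. The article supports only that no other is named in it; the full protocol or analysis plan could add sensitivity analyses.
- A reader might infer that the error favours the device, for example through sham subjects leaving for lack of effect. The documents say nothing about who leaves, or even that pain will fall in both arms. More dropout in the device arm would bias against the device. Nor does lack-of-effect dropout reliably produce the bias: when the three sham subjects with the smallest true improvement left after V3, the bias was −0.1 mm and type I error 4.7%. When the three with the worst observed change at V3 left, they were 3.5 mm and 5.6%.
- The raised error rates need lopsided dropout. With six dropouts at equal risk, the chance that all fall in the sham arm is about 0.8%. A 4 versus 2 split gave 1.7 mm and 4.3%.
- Section 2.7 may reduce missingness. With half the outcomes retrieved, 3 versus 0 gave 1.4 mm and 5.2%, and 6 versus 0 gave 2.6 mm and 7.7%.
- The bias is modest against the pilot's precision: 2 to 2.8 mm is 0.4 to 0.6 of the 4.7 mm SE. The residual SD rose by only 5 to 9%, well within the sampling error of an SD from 30 subjects. The article itself calls the sample too small for firm conclusions.

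These points limit the size and remove any claim about direction. They do not make LOCF a sound main method: it still assumes flat scores after dropout, and with equal dropout it still weakens a true effect when pain is improving.

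**Conclusion.** The point holds as a recommended change. LOCF is the missing-data method the article names, dropout of 20% is allowed for, and repeated scores that support a better method are already collected.

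Under the assumed trajectory, the planned level of dropout shrinks a 15 mm effect by about 2 mm and costs about 22 percentage points of power (85% to 63%), without inflating type I error. A false difference needs dropout, or its timing, to differ between arms: about 2.7 mm for 3 versus 0, and about 5.3 mm for the extreme 6 versus 0. All these sizes depend on the assumed improvement, SD, correlation, dropout time and dropout mechanism, none of which the article gives, and they fall if outcomes are retrieved. The documents do not support saying that the result will be biased towards the device, or that the pilot's SD will be materially distorted.

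**What to change.** Replace the LOCF sentence in section 2.8 with a linear mixed model for VAS, PPT and ODI, each fitted to the values from V2 to V7. Include group, visit, group-by-visit and the V1 value as covariate, with a parsimonious covariance structure suited to 30 subjects. Use every observed value, including those obtained after dropout. Keep LOCF as a sensitivity analysis only.

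Report the group contrast at V7 for PPT and ODI, which section 2.6 already ties to V7. For VAS, report it at the time point the sponsor sets as primary. V7 is the natural match, but section 2.6 does not set it, so this should be an explicit decision. PGIC is ordinal and lies outside this model.

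The cost is a change of wording and a little more programming; the MIXED procedure in the named SPSS package can fit the model. The sample size stays at 30. The downside is that the model relies on missing-at-random, which the data cannot confirm, and needs a simple covariance structure at this size.

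### Section 2.8 assigns the paired McNemar test to categorical variables with no within-subject qualifier, in a trial of two independent arms

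*Protocol article*

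**What the plan says.** Section 2.1 of the protocol article gives the design: "This study was designed as a randomized single-blinded, sham-controlled, parallel-group, pilot clinical trial". Patients "will be randomly assigned to groups in a 1:1 ratio", and Section 2.3 adds "An independent statistician will randomly assign 15 individuals per group", in balanced blocks without stratification. Neither section describes matching or crossover.

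Section 2.8 takes efficacy first: ANCOVA for VAS with baseline as covariate, and the other efficacy variables handled the same way. It then turns to safety. After naming the safety population it gives three sentences on tests:

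- continuous variables: independent-sample t-test or Wilcoxon rank-sum test;
- categorical variables: "The McNemar test will be used for the analysis of categorical variables";
- association of treatment with adverse events: chi-squared or Fisher exact test.

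The McNemar sentence names no variable, no pair of time points and no restriction to within-subject comparisons.

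**The concern.** McNemar compares two binary readings that belong together, usually on the same subject before and after. The two arms here contain different, unmatched people. Between the arms the test can be run only by inventing pairs or by feeding it the wrong table, and the P-value then has no valid meaning. Within one arm it is a legitimate test of change, but it does not address the objective given in the Introduction, which is LSM-01 compared with sham. On that reading Section 2.8 names no between-arm test for categorical variables other than adverse events.

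At stake are the categorical results that fall under this sentence. An analyst following it literally would report either an invalid comparison or two separate within-arm tests that invite an indirect one.

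**Working it through.** **Inputs from the protocol article.** Section 2.1: "the empirically optimal sample size is 12 individuals per group" and "Considering a dropout rate of 20%, the calculated sample size for this pilot clinical trial is 30". Section 2.8: "In all statistical tests, an α = 0.05 on both sides will indicate a statistically significant difference".

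**Plan's own figure.** 12 / (1 − 0.20) = 15 per arm; 2 × 15 = 30. The stated total is reproduced, and n = 15 per arm is used below.

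**Assumption.** The document gives no event rates for any categorical variable. Every count and rate below is illustrative.

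**Formula.** With discordant counts b and c, exact two-sided McNemar P = min[1, 2 × Pr(X ≤ min(b, c))], where X ~ Binomial(b + c, 0.5).

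**1. Between arms, with invented pairs.** Take 2/15 events in one arm and 8/15 in the other. Fisher's exact test: 2 × (3003 + 75075 + 675675) / 30045015 = 0.050. For McNemar, let k be the number of artificial pairs in which both members have the event. Then b = 2 − k and c = 8 − k:

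| k | (b, c) | Exact McNemar P |
|---|---|---|
| 2 | (0, 6) | 2 × 1/64 = 0.031 |
| 1 | (1, 7) | 2 × 9/256 = 0.070 |
| 0 | (2, 8) | 2 × 56/1024 = 0.109 |

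The data are the same in each row. Only the line-up of unrelated patients differs, and the result falls on either side of 0.05.

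**2. Between arms, applied to the arm-by-response table.** McNemar then compares non-responders in one arm with responders in the other.

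- 12/15 versus 12/15: b = 3, c = 12, P = 2 × 576/32768 = 0.035; Fisher P = 1.0.
- 12/15 versus 3/15: b = 3, c = 3, P = 1.0; Fisher P = 0.003.

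Exact enumeration at 15 per arm gives these rejection rates at two-sided 0.05:

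| True response rates | McNemar | Fisher |
|---|---|---|
| 0.1 vs 0.1 | 0.97 | 0.0055 |
| 0.2 vs 0.2 | 0.62 | 0.017 |
| 0.3 vs 0.3 | 0.18 | 0.017 |
| 0.5 vs 0.5 | 0.002 | 0.017 |
| 0.7 vs 0.3 | 0.006 | 0.43 |
| 0.8 vs 0.2 | 0.006 | 0.87 |

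**3. Within each arm, before versus after.** The test is valid for its own question. Suppose both arms have the same true change, with a chance of worsening of 0.05. Let w be the chance that one arm reaches P ≤ 0.05. Exactly one arm is then significant with probability 2w(1 − w):

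- chance of improvement 0.3: w = 0.167, giving 0.28;
- 0.5: w = 0.596, giving 0.48;
- 0.6: w = 0.770, giving 0.35.

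Reading the two within-arm results against each other would therefore often suggest an arm difference where none exists.

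**4. PGIC.** Section 2.6.4 gives seven ordered answers that already describe change from baseline, and Table 1 schedules PGIC only from V2. It is not binary and has no baseline value. McNemar has nothing to pair, and baseline-adjusted ANCOVA has no covariate to use.

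**The case against.** The strongest reply is that the sentence sits in the safety part of Section 2.8. The authors name correct independent-group tests when they state a treatment comparison (adverse events), so naming a paired test just before could mean a within-subject safety shift. Table 1 does schedule repeated checks, such as vital signs and changes in drug treatment. On that reading the P-values are valid, and not comparing arms is simply what a paired test does. This reading is possible. But the text does not state it, names no binary before/after variable, and places the sentence directly after independent-sample tests for continuous variables. Even if it was intended, the qualifier is needed.

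Three stronger inferences are tempting and are not supported:

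- *That a between-arm use is certainly meant.* The neighbouring sentences suggest it, but they do not settle it.
- *That McNemar is the planned test for PGIC.* PGIC is a secondary efficacy outcome, and Section 2.8 sends efficacy variables to the same analysis as VAS. That rule does not fit PGIC either, but it is a different rule.
- *That every categorical comparison apart from adverse events is compromised.* The document does not list which variables fall under the sentence, so the number affected may be small.

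It is also fair to object that the numerical examples come from assumed rates and that the document plans no artificial pairing. They show the nature of the mismatch and do not predict an error in this trial. Unequal arms after dropout would add a further obstacle to pairing, but carrying the last observation forward could keep arm sizes equal, so nothing here relies on that.

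**Conclusion.** The sentence is wrong as written for a parallel-group trial. Between arms McNemar is invalid; within an arm it does not compare LSM-01 with sham. That conclusion rests on the design and on the definition of the test, and not on the assumed rates.

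Its reach is probably categorical safety variables, plus any other categorical variables apart from adverse events. A reader might infer that the trial's main results are at risk, but the documents do not support that: the primary VAS analysis is ANCOVA, and adverse events are compared by chi-squared or Fisher's exact test. Section 3 also says that this pilot is too small for firm conclusions on effectiveness. The point should be fixed, but it is not critical to the trial.

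**What to change.** Replace the McNemar sentence in Section 2.8 with: *Categorical variables will be compared between groups by chi-squared or Fisher exact test, and ordinal variables by Wilcoxon rank-sum test.*

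List PGIC explicitly under the rank-sum test, as an exception to the rule that efficacy variables follow the VAS analysis.

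Keep McNemar only if a within-subject binary before/after shift is really intended. In that case name the variable and the two time points, and label the result descriptive.

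The cost is one replaced sentence and the PGIC entry. Data collection, randomisation and the sample size of 30 do not change.
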